## Abstract

**Introduction:**

Older adults with an acute moderate-to-severe lower respiratory tract infection (LRTI) or pneumonia are generally treated in hospitals causing risk of iatrogenic harm such as functional decline and delirium. These hospitalisations are often a consequence of poor collaboration between regional care partners, the lack of (acute) diagnostic and treatment possibilities in primary care, and the presence of financial barriers. We will evaluate the implementation of an integrated regional care pathway (‘The Hague RTI Care Bridge’) developed with the aim to treat and coordinate care for these patients outside the hospital.

**Methods and analysis:**

This is a prospective mixed methods study. Participants will be older adults (age≥65 years) with an acute moderate-to-severe LRTI or pneumonia treated outside the hospital (care pathway group) versus those treated in the hospital (control group). In addition, patients, their informal caregivers and treating physicians will be asked about their experiences with the care pathway. The primary outcome of this study will be the feasibility of the care pathway, which is defined as the percentage of patients treated outside the hospital, according to the care pathway, whom fully complete their treatment without the need for hospitalisation within 30 days of follow-up. Secondary outcomes include the safety of the care pathway (30-day mortality and occurrence of complications (readmissions, delirium, falls) within 30 days); the satisfaction, usability and acceptance of the care pathway; the total number of days of bedridden status or hospitalisation; sleep quantity and quality; functional outcomes and quality of life.

**Ethics and dissemination:**

The Medical Research Ethics Committee Leiden The Hague Delft (reference number N22.078) has confirmed that the Medical Research Involving Human Subjects Act does not apply to this study. The results will be published in international peer-reviewed journals.

**Trial registration number:**

ISRCTN68786381.

STRENGTHS AND LIMITATIONS OF THIS STUDYA major strength of this study is that the care pathway has been co-designed by patients from the start, and their interests were the mainstay in the development of the care pathway.The satisfaction of patients, their informal caregivers and physicians will be evaluated.This study evaluates the real-life application of the care pathway, which ensures that findings can be used immediately to improve the care pathway.The mixed methods design of the study enables us to get insight into the feasibility, usability and acceptance of the care pathway, although the sample size of this study will be relatively small for measuring effectiveness and safety.The success of the care pathway partially depends on non-medical issues, such as the availability and capacity of homecare institutions and nursing homes.

## Introduction

An acute moderate-to-severe lower respiratory tract infection (LRTI) or pneumonia in older adults is generally characterised by diagnostic uncertainty, a high risk of complications and negative outcomes, including mortality.^1 2^ Care in the home situation often acutely falls short because of increased dependency due to falls, decline in activities in daily living (ADL) or a state of confusion. This often leads to a presentation at the emergency department (ED) with the goal to define the optimal treatment plan which usually consists of a combination of antimicrobials, oxygen suppletion and/or inhalation medication, treatment and/or prevention of delirium, and additional help in ADL; and the optimal treatment location. Although, these treatments can be organised outside the hospital, for example, at home or in a nursing home, hospitalisation often occurs because of the 24/7 open access of EDs, and treatment outside the hospital is often considered irresponsible or impossible due to difficulties in ADL and the lack of (available) care.^3–6^

Such hospitalisations of older adults can be considered unnecessary or avoidable when they are related to poor transmural collaboration and different treatment protocols between regional care partners (general practitioners (GPs), hospitals, nursing homes and homecare institutions), the lack of diagnostic and treatment possibilities in primary care, the lack of (acute) availability and capacity in nursing homes and homecare, or the presence of financial barriers.^7–11^ Especially in older adults, hospitalisations are associated with iatrogenic harm such as delirium, falls and functional decline.^12–14^ As a consequence, older patients often show further decline in ADL from these hospitalisations, and as a result are often transferred to a nursing home or revalidation centre for further recovery. We hypothesise that these hospitalisations may be avoided when the care is well coordinated between care partners.

We, therefore, developed a multidisciplinary regional care pathway ‘The Hague RTI Care Bridge’, to support GPs with the diagnostics, treatment and organisation of care for older adults with an acute moderate-to-severe LRTI or pneumonia.^15^ In this care pathway, clear collaboration agreements were made between involved regional care partners. Three patient journeys were embedded in the care pathway (Figure 1 and Table 1): a hospital-at-home treatment, an ED presentation with priority assessment and admittance to a readily available recovery bed in a nursing home. The care pathway includes a detailed guide on treatment (eg, antibiotics, oxygen suppletion) and its monitoring.^15^

**Figure 1 F1:**
[figure not shown]
The three patient journeys in the care pathway. ED, emergency department; RTI, respiratory tract infection.

**Table 1 T1:** Overview of the three patient journeys in the care pathway

	Hospital-at-home treatment	Presentation at the emergency department	Temporary admission in a nursing home
Treatment location	Home	Three options: Home (pathway) Nursing home (pathway) Hospital (regular care)	Nursing home
Treatment	Possibilities: Antimicrobials (oral or intramuscular) Oxygen suppletion Inhalation medication Home care	Possibilities: Antimicrobials (oral or intravenous) Oxygen suppletion Inhalation medication Hospital care	Possibilities: Antimicrobials (oral or intramuscular) Oxygen suppletion Inhalation medication Multidisciplinary care
Treating physician	General practitioner	Treating physician at ED (and ward when admitted)	Elderly care physician
Monitoring	Home monitoring with monitoring kit and registration form (vitals three times a day)	Depends on chosen treatment location*	Monitoring conform the standard of care in the nursing home

*Hospitalised patients will receive the local standard of care.

ED, emergency department.

In this prospective mixed methods study, the implementation of the care pathway will be evaluated. During this 12-month study period, it is hypothesised that in at least 75% of the older adults with an acute moderate-to-severe LRTI or pneumonia who are treated outside the hospital according to the care pathway, hospitalisation can be avoided.

### Objectives

#### Primary objective

The primary objective is to determine the feasibility of the care pathway, which is defined as the percentage of patients treated outside the hospital, according to the care pathway, whom fully complete their treatment without the need for hospitalisation within 30 days of follow-up.

#### Secondary objectives

The secondary objectives are to determine the safety of the care pathway (30-day mortality and occurrence of complications (readmissions, delirium, falls) within 30 days); the satisfaction, usability and acceptance of the care pathway; the total number of days of bedridden status or hospitalisation; sleep quantity and quality; functional outcomes and quality of life (QoL).

## Methods and analysis

### Study design

The design of the study is a prospective mixed methods study, which will be performed in the urban area of The Hague, the Netherlands. In the Netherlands, over 35000 adults are hospitalised with an acute LRTI or pneumonia annually, including 1500–2000 hospitalisations in the area of The Hague. The study period will be from 1 December 2022 to 30 November 2023. In this period, the results will be evaluated frequently for the benefit of interim adjustments.

This is a multicentre study including two teaching hospitals (Haga Teaching Hospital and Haaglanden Medical Center), the largest GP care group and the two biggest homecare institutions of The Hague. The setting will primarily be outside the hospital (primary care or nursing homes). The care pathway offers GPs three options (Figure 1 and Table 1) for the treatment of older adults with a clinical diagnosis of an acute moderate-to-severe LRTI or pneumonia.

### Study population

The study population consists of older adults (age≥65 years) who visit their GP or present at the ED with a clinical diagnosis of an acute moderate-to-severe LRTI or pneumonia. The informal caregivers and treating physicians of participating patients will also be asked to participate in this study to evaluate their experiences and satisfaction about the received or given care.

### Eligibility criteria

To be eligible to participate, a patient must meet all the following criteria: age≥65 years, clinical diagnosis of an acute moderate-to-severe (Pneumonia Severity Index (PSI) class≥3 or Confusion, Urea, Respiratory rate, Blood pressure and age≥65 years (CURB-65) score≥2) LRTI or pneumonia, an oxygen saturation≥92% and a respiratory rate≤24 breaths/minute with a maximum of 5 liters of oxygen (or adjusted oxygen saturation cut-offs as clinically indicated (eg, for patients with chronic obstructive pulmonary disease) by the physician) and written informed consent (IC) for participation.^16 17^ Exclusion criteria are: chemotherapy for solid organ malignancy (<2 months before presentation), active haematologic malignancy, immunocompromised status (eg, solid organ transplants) and/or severe dementia (Clinical Dementia Rating Scale Sum Of Boxes score 16–18).^18^ To be eligible to participate, an informal caregiver must meet all the following criteria: age≥18 years, being an informal caregiver of a patient included in the study and written IC for participation. To be eligible to participate, a treating physician must meet all the following criteria: physician of a patient included in the study at the main location of treatment, the physician should have treated the patient for at least≥2 (consecutive) days and written IC for participation.

Due to logistical limitations (absence of own GPs and evening/night/weekend shifts in nursing homes), the care pathway will be active on weekdays (Monday–Friday) between 08.00 and 18.00 hours for the hospital-at-home treatment and every day (Monday–Sunday) between 08.00 and 20.00 hours for the admission on a recovery bed in a nursing home. Patients who present at their GP and/or at the ED with an acute LRTI or pneumonia when the care pathway is active will be eligible to be treated according to the care pathway. Patients with an acute LRTI or pneumonia who are hospitalised subsequently to this ED presentation will receive the local standard of hospital care and will therefore not be included.

#### Control group

Patients who fulfil the inclusion criteria and do not meet the exclusion criteria of the care pathway, and are hospitalised on weekdays outside office hours (18:00–08:00 hours) or weekend days due to inactivity of the care pathway, will serve as a control group.

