Despite its strengths, this study does have some limitations. First, the success of the care pathway partially depends on non-medical issues, such as the availability and capacity of nursing homes and homecare. During the course of this study, these barriers will be evaluated and adjustments will be made if necessary. Another limitation is that the allocation between the care pathway group and the hospital group is based on the time of day and day of the week. Research has shown that illness severity is generally greater outside office hours.^46^ Though, we aim to limit this bias by using limits for oxygen saturation, respiratory rate and maximum of oxygen suppletion in the inclusion criteria, the data of clinical outcomes should therefore be interpreted with caution and be considered explorative rather than proof. Furthermore, it will be challenging to keep all healthcare professionals informed as the care pathway is implemented in an urban area where many healthcare professionals are active. The mixed methods design of the study enables us to get insight in the feasibility, usability and acceptance of the care pathway, although the sample size will be relatively small for measuring effectiveness.

In summary, The Hague RTI Care Bridge will improve our understanding of the possibility and the feasibility to treat patients with an acute moderate-to-severe LRTI or pneumonia outside the hospital. In addition, it will give insight in this new cooperation between two teaching hospitals, the largest GP care group and the two biggest homecare institutions of The Hague, thereby creating possibilities for a similar outpatient treatment for patients with other medical problems (eg, erysipelas and urinary tract infections).

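### The control-group window covers 34 hours a week in which the nursing-home route of the pathway is open, and the eligibility text can be read as excluding the same patients

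*Protocol article*

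**What the plan says.** The Eligibility criteria section gives two sets of operating hours. Hospital-at-home is "active on weekdays (Monday–Friday) between 08.00 and 18.00 hours for the hospital-at-home treatment". The nursing-home route runs "every day (Monday–Sunday) between 08.00 and 20.00 hours for the admission on a recovery bed in a nursing home". Patients who present "when the care pathway is active will be eligible to be treated according to the care pathway". The section then says that patients "who are hospitalised subsequently to this ED presentation will receive the local standard of hospital care and will therefore not be included".

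The Control group section takes as controls those who meet the pathway's inclusion and exclusion criteria and "are hospitalised on weekdays outside office hours (18:00–08:00 hours) or weekend days due to inactivity of the care pathway".

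The Discussion lists as a limitation that the "allocation between the care pathway group and the hospital group is based on the time of day and day of the week". The Data analysis plan establishes the secondary outcomes by comparing the pathway group with this control group.

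**The concern.** The control window is the complement of the hospital-at-home hours, not of the hours in which any part of the pathway is open. On weekday evenings until 20:00 and on weekend days until 20:00, a recovery bed in a nursing home is still an available route. Take an eligible patient hospitalised from the emergency department on Saturday at 14:00 or Tuesday at 19:00. The Control group section places this patient in the control window. The end of the Eligibility criteria can be read as leaving the patient out of the study.

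The comparison depends on the clock, and not the patient's condition, deciding who is a control. In the overlap hours, two eligible patients arriving in the same hour can enter opposite groups, one through a recovery bed and one through hospital admission. What separates them may be clinical judgement, preference or bed capacity. The article itself says that the pathway's success depends partly on nursing-home and homecare capacity. Mortality, complications, function and quality of life are all compared between these groups, so selection of this kind could bias those comparisons.

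**Working it through.** The article states no figure for the overlap, so there is none to reproduce. The count below uses its own clock times over a 168-hour week.

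**Inputs**
- Control window (Control group): weekdays 18:00–08:00 and weekend days.
- Hospital-at-home hours (Eligibility criteria): Monday–Friday 08:00–18:00.
- Nursing-home hours (Eligibility criteria): every day 08:00–20:00.
- Planned controls (Sample size): 50.

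**Hours per week**
- Control window: 5 × 14 + 2 × 24 = 70 + 48 = 118 h.
- Hospital-at-home: 5 × 10 = 50 h. None of these fall in the control window (118 + 50 = 168).
- Nursing-home route: 7 × 12 = 84 h.
- Control window with the nursing-home route open: 5 × 2 + 2 × 12 = 10 + 24 = 34 h.
- Share of control time: 34 / 118 = 28.8%.
- Control time with no route open: 118 − 34 = 84 h (20:00–08:00 every day).

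**Alternative reading of the weekday window.** If it means nights that start on Monday to Friday, Monday 00:00–08:00 drops out. The window is then 118 − 8 = 110 h and the overlap 34 / 110 = 30.9%.

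**Share of patients.** Hours are not patients. Let k be the hourly rate of eligible admissions in 08:00–20:00 divided by the rate in 20:00–08:00. The expected share of controls from overlap hours is 34k / (34k + 84). The article does not give k, so a range is assumed:

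| k (assumed) | Share of controls | Of 50 planned controls |
|---|---|---|
| 0.5 | 17 / 101 = 16.8% | about 8 |
| 1 | 34 / 118 = 28.8% | about 14 |
| 1.5 | 51 / 135 = 37.8% | about 19 |
| 2 | 68 / 152 = 44.7% | about 22 |
| 3 | 102 / 186 = 54.8% | about 27 |

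These shares count everyone hospitalised in the overlap hours. Hospital-at-home is closed in all 34 of them, so some of these patients may have been hospitalised because the route that suited them was shut. The table is therefore an upper bound on controls passed over for an open route.

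**The case against.** The strongest reply is that the text can be read without contradiction. The Control group section does not only list hours. It also gives inactivity of the pathway as the reason for hospitalisation. Read as a condition, that removes a patient who could have had a recovery bed and was hospitalised by choice. Likewise, the exclusion at the end of the Eligibility criteria may mean only that such a patient is not in the pathway group. A reader might infer that the article provably makes one patient both excluded and a control, but the documents do not support anything that firm. What remains is that on the first reading the listed hours are too wide, on the second the overlap is untouched, and no sentence says which is meant. The Discussion's description of allocation by time and day favours taking the hours at face value.

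A reader might also infer that every overlap control had an open route and was not placed in it. That is not supported either. For a patient suited to home treatment, the stated inactivity is true on a Saturday afternoon. The section has no rule separating that patient from one for whom an open nursing-home route was not used.

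A third tempting inference is that the overlap makes the pathway look safer. It is plausible that hospitalised patients are sicker or more dependent, but the article does not show it. Controls must meet the same limits on saturation, respiratory rate and oxygen, which the Discussion names as its means of limiting severity bias. Those limits do not remove selection among patients who all satisfy them, so the risk stands without a proven direction.

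Finally, the Discussion already calls the clinical outcomes explorative and acknowledges greater severity outside office hours. That lowers the stakes. It does not address patients hospitalised while a pathway route was open.

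**Conclusion.** The point holds as an unreconciled conflict between two stated rules. The control window follows one route's closing hours while the stated reason refers to the pathway as a whole. The overlap of 34 of 118 h a week (28.8%, or 30.9% on the alternative reading) follows from the article alone. The share of controls could be below or above that figure, from about 17% to 55% over assumed day-to-night ratios of 0.5 to 3, so 29% should not be read as a minimum for patients.

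In those hours, membership of the control group need not be settled by clock time alone, contrary to the Discussion. The secondary between-group comparisons may be biased by an unknown amount. The primary outcome is a percentage in the pathway group and its power calculation is one-sample, so neither uses the controls. Because only comparisons already labelled explorative are affected, this should be fixed but does not threaten the main result.

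**What to change.** State one rule for which route's inactivity defines a control, and align the last sentence of the Eligibility criteria with it, making clear whether those patients are outside the study or only outside the pathway group. The rule should also say which clock time counts, since the Eligibility criteria refer to presentation and the Control group section to hospitalisation.

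Record presentation time for every patient. Report the between-group comparisons with and without controls hospitalised on weekdays 18:00–20:00 or weekends 08:00–20:00.

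The cost is a sentence or two of text, one data item and one additional analysis. Control data already come from the hospital electronic records, so the extra item should be a small burden.

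The restricted comparison has a real downside. With 50 controls it would keep about 42 at k = 0.5, 36 at k = 1, 28 at k = 2 and 23 at k = 3. All would be from 20:00–08:00, where the Discussion's caveat about out-of-hours severity applies most directly. It would also drop controls who were hospitalised because hospital-at-home was closed. For these reasons, limiting recruitment to the night hours is a trade-off and not an obvious correction. Both results should be shown and read with that caveat.

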### Sample size

Ideally, 50 patients will be treated outside the hospital (care pathway group) and 50 patients will be treated in the hospital (control group). A power analysis was performed for the evaluation of the feasibility of the care pathway. In clinical practice, approximately 10% of the hospitalised patients are readmitted to the hospital after discharge. Our hypothesis is that in at least 75% of the older adults with an acute LRTI or pneumonia who are treated outside the hospital (at home or in a nursing home) according to the care pathway (care pathway group), hospitalisation can be avoided (complete treatment outside the hospital during 30-day follow-up). An 80% power with an alpha of 0.05 for an one-sample study will be achieved if 40 patients are recruited for the care pathway group.

For the qualitative endpoints, data collection (interviews) will be performed until data saturation is reached. When a patient is included and his/her informal caregiver and/or treating physician does not want to participate or cannot participate in the study, the patient will remain in the study and no extra patient will be included to make up for the missing informal caregiver and/or physician.

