### Data analysis plan

The primary outcome is the feasibility of the care pathway. This will be quantitative data. Categorical variables will be presented as counts and frequencies. The quantitative data will be analysed with the Statistical Package for the Social Sciences (SPSS) V.28.

The secondary outcomes will be established by comparing the patients in the care pathway group with the patients in the control group during follow-up. Secondary outcomes are the safety of the care pathway (30-day mortality and occurrence of complications within 30 days); the satisfaction, usability and acceptance of the care pathway; the total number of days of bedridden status or hospitalisation; sleep quantity and quality; functional outcomes and QoL.

Categorical variables will be presented as counts and frequencies. Differences between groups will be tested with χ^2^ tests and multivariate logistic regression models. Continuous data will be presented as means (standard deviations) for normally distributed data or medians (interquartile ranges) for non-normally distributed data. Differences between groups will be tested with independent t-tests or one-way Analysis Of Variance (ANOVA) tests (normal distribution), or Mann-Whitney U or Kruskal-Wallis tests (no normal distribution) depending on the amount of groups to be compared per analysis, and by multivariate linear regression models. All tests of significance will be at two-tailed 0.05 level. The 95% confidence intervals will be used to assess the presence/absence of associations. The quantitative data will be analysed with SPSS V.28.

All recorded interviews will be transcribed by two research team members and hereafter then coded with Atlas.ti V.22. The interview recordings will be saved in a secured folder on the network of the coordinating hospital and will be deleted after verbatim transcription. Transcriptions will be saved on the network of the coordinating hospital. We will apply thematic content analysis to identify and categorise recurrent themes/elements in the interviews. Thereby, we aim to classify the qualitative data in the right sections (implementation, methods, context) of the process evaluation of the implementation of the care pathway.

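### The 80% power claimed with 40 patients is reached only by reversing the 75% hypothesis or by a one-sided test that conflicts with the plan's two-tailed rule

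*Protocol article*

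**What the plan says.** The Sample size section of the protocol article introduces a power analysis for feasibility, the primary outcome. It gives two rates. The first is background: "approximately 10% of the hospitalised patients are readmitted to the hospital after discharge". The second is the hypothesis: "Our hypothesis is that in at least 75% of the older adults with an acute LRTI or pneumonia who are treated outside the hospital", hospitalisation can be avoided over 30 days. It then concludes: "An 80% power with an alpha of 0.05 for an one-sample study will be achieved if 40 patients are recruited" for the pathway group. The section also sets an ideal target of 50 patients per group. It does not say which rate is the null, which is the alternative, or whether the test is one- or two-sided.

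The Data analysis plan states: "All tests of significance will be at two-tailed 0.05 level". For the primary outcome it names no test: "The primary outcome is the feasibility of the care pathway. This will be quantitative data. Categorical variables will be presented as counts and frequencies".

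**The concern.** This is the only power statement in the article, and it concerns the primary outcome. A reader will take it to mean that 40 patients give an 80% chance of supporting the 75% hypothesis. The only two-tailed calculation with the section's own rates that returns 40 makes 75% the alternative to be detected and 90% the null. Rejecting that null would show that the pathway falls short of 90%, not that it reaches 75%.

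The 10% is also a different event from the primary outcome. It counts readmission after discharge among patients already treated in hospital, whereas the outcome is hospitalisation among patients being treated outside hospital. The section gives no reason why one should serve as null or expected value for the other.

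At stake is how the result will be read. For example, 32 of 40 (80%) could be presented as meeting the 75% hypothesis in a study with 80% power. Yet if the true rate were 75%, 32 or more successes in 40 would occur with probability 0.30 (exact binomial upper tail).

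**Working it through.** **Inputs.** From Sample size: alpha 0.05, power 80%, one sample, n = 40 (target 50), 10% readmitted (90% not), hypothesis of at least 75% avoided (25% hospitalised). From Data analysis plan: two-tailed 0.05.

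**Formula** (one-sample proportion, normal approximation):

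n = [(z_α √(p0(1−p0)) + z_β √(p1(1−p1))) / (p1−p0)]², with z_β = 0.8416, √(0.9×0.1) = 0.3000, √(0.75×0.25) = 0.4330, and a difference of 0.15 throughout.

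**Reproducing the stated 40**

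- (a) Null 90%, alternative 75%, two-sided (z_α = 1.96): [(1.96×0.3000 + 0.8416×0.4330)/0.15]² = 40.3. Power at n = 40 is 79.8%.
- (b) Null 75%, true rate 90%, one-sided 5% (z_α = 1.645): [(1.645×0.4330 + 0.8416×0.3000)/0.15]² = 41.4. Power at n = 40 is 78.5% by the normal approximation. Exactly, 35/40 are needed (attained alpha 0.043) and power is 79.4%.

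Both are close enough to the stated figure to be its source. Other approximations do not open a third route. The arcsine formula gives 82% at n = 40 one-sided and 72% two-sided. A continuity-corrected, one-sided version of (a) gives n = 39.1, but it has the reversed null and is one-sided as well.

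**In the direction of the hypothesis, under the two-tailed rule.** Null 75%, true rate 90%, z_α = 1.96: [(1.96×0.4330 + 0.8416×0.3000)/0.15]² = 53.9, so about 54 patients. Normal-approximation power is 63.1% at n = 40 and 76.0% at n = 50.

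**Exact binomial check.** The test succeeds at the smallest count whose upper-tail probability at 75% is no more than 0.025.

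| | n = 40 | n = 50 |
|---|---|---|
| Successes needed | 36 | 44 |
| Upper-tail alpha | 0.016 | 0.019 |
| Power, true rate 85% | 26% | 36% |
| Power, true rate 90% | 63% | 77% |
| Power, true rate 92% | 79% | 90% |
| Power, true rate 95% | 95% | 99% |

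**Precision as an alternative.** If 40 of 50 (80%) avoid hospitalisation, the exact (Clopper-Pearson) 95% confidence interval is 66% to 90%.

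**The case against.** The strongest reply is that the section never assigns roles to its rates, so the reversed null is a reconstruction. Calculation (b) has the right direction and comes within a point of 80%. This stands: a reader might infer that the sponsor powered the study for the wrong hypothesis, but the document does not establish it. If (b) was used, however, the figure depends on a one-sided test.

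On sidedness, the two-tailed sentence sits in the paragraph on differences between groups, after the secondary outcomes are introduced, so it may not have been meant for the primary outcome. That is possible. But its wording covers all tests, and no exception for the primary outcome is stated, so the two sections at least need reconciling.

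A reader might also infer that power cannot exceed 63%. That is not supported. The 63% belongs to 40 patients and a true rate of 90%; power is 79% at 92%, and the intended 50 patients give 77% at 90%. Nor is it a fault of this plan that, at a true rate of exactly 75%, a test against 75% would rarely reject. That is true of any superiority test at its null.

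A third rate could have been used as null: about 54% against 75%, two-sided, gives 79% at n = 40. Nothing in the article points to such a rate.

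Finally, the article condenses a fuller protocol, the primary analysis is descriptive, and no stated decision hangs on a p-value. This lowers the consequences and means that missing detail alone would be no finding. The point here is a stated number that does not fit the stated rates, hypothesis and testing rule together.

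**Conclusion.** Wrong as written. With the two rates the section provides, 80% power at 40 patients needs either a null of 90%, which reverses the hypothesis, or a one-sided 0.05 test, which conflicts with the two-tailed rule. Which of the two was used cannot be determined from the article, and neither leaves the statement consistent with the rest of the plan.

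Under the two-tailed rule, with 75% as null and 90% as the true rate, the 80% becomes about 63% at 40 patients. The intended 50 narrow the gap but do not close it at that rate. The size rests on the assumed 90%, whose only source in the document is the readmission figure; between true rates of 85% and 92%, power at 40 patients runs from 26% to 79%.

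**What to change.** Replace the power sentence in one of two ways.

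1. **Keep a power statement.** Give the null (75% or less avoid hospitalisation), the assumed true rate with a justification of its own rather than the readmission-after-discharge figure, and a sidedness consistent with the Data analysis plan. Restate the power for the 50 patients already intended: 77% if the true rate is 90%, 36% if it is 85% (exact binomial, two-sided 0.05, 44/50 needed).
2. **Drop the power claim.** Since the primary analysis is descriptive, state the expected precision for 50 patients instead, for example the 66% to 90% interval that 40/50 would give.

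Either change is wording only and needs no patients beyond the 50 intended. The cost is a less favourable stated figure: under the first option, 80% power would be claimed only if a true rate above 90% can be justified.
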